| IOP | Intraocular Pressure |
| ISF | Investigator site file |
| ITT | Intention to treat |
| KKS | Coordination Center for Clinical Trials (Koordinierungszentrum für Klinische Studien) |
| LKP | Clinical Trial Director according to AMG (Leiter der Klinischen Prüfung) |
| LSI | Last subject in |
| LSO | Last subject out |
| MedDRA | Medical dictionary for regulatory activities terminology |
| OCT | Optical Coherence Tomography |
| SAE | Serious adverse event |
| SAP | Statistical analysis plan |
| SDV | Source data verification |
| SUSAR | Suspected unexpected serious adverse reaction |
| TMF | Trial master file |

Synopsis

| Title | Investigation of the efficacy and safety of preoperative IOP reduction with preservative-free COSOPT-S® (dorzolamide/timolol, MSD) eye drops versus oral acetazolamide and dexamethasone eye drops and assessment of the clinical outcome of trabeculectomy in glaucoma patients |
| --- | --- |
| Short title | COSOPT-S®  Study |
| EudraCT | 2010-019975-30 |
| Sponsor trial code | 35131 |
| Indication | Glaucoma requiring trabeculectomy |
| Phase | IV |
| Treatments | Test product: COSOPT-S® (dorzolamide/timolol, MSD) eye drops b.i.d.  Reference therapy: oral acetazolamide 250 mg - 1500mg (DIAMOX®) per day (two or three doses), Preservative-free dexamethasone 1mg/ml eye drops five times per day |
| Primary objective | - To demonstrate that COSOPT-S® b.i.d is not inferior to the standard regimen in terms of IOP reduction three months after trabeculectomy. |
| Secondary objectives | - To show that the tolerability and safety of COSOPT-S® b.i.d. is descriptively superior to that of reference therapy - Comparison of the regimen COSOPT-S® b.i.d. with the reference regimen in terms of postoperative complications and the filtration bleb status three months after trabeculectomy - Exploration of patients’ satisfaction |
| Trial design | A prospective, active-controlled, open-label, randomized monocentric parallel group study |
| Trial population | Main inclusion criteria:  Subjects meeting all of the following criteria will be considered for enrolment to the trial:   - Male or female patients aged 18 years or older - Caucasian - A clinical diagnosis of open angle glaucoma, pseudoexfoliation or pigment dispersion glaucoma, or ocular hypertension in one or both eyes - Planned trabeculectomy - Previous treatment with antiglaucoma agents containing preservatives for at least one month - Best corrected visual acuity of 20/800 or better in the study eye   Main exclusion criteria:  Subjects presenting 1or more of the following criteria will not be enrolled in the trial:   - Secondary glaucoma except pseudoexfoliation glaucoma and pigmentary glaucoma - Current ocular infection, i.e. conjunctivitis or keratitis - Any abnormality preventing reliable applanation tonometry - Intraocular surgery or laser treatment within the past three months - History of surgery involving the conjunctiva - History of cataract surgery with sklerocorneal approach - Subject is allergic to sulfonamides - Reactive airway disease, including bronchial asthma or a history of bronchial asthma, or severe chronic obstructive pulmonary disease - Sinus bradycardia, second or third degree atrioventricular block, overt cardiac failure, cardiogenic shock - Severe renal dysfunction (CrCl < 30 ml/min) or hyperchloraemic acidosis - Depressed blood levels of sodium and / or potassium - Marked kidney and liver disease or dysfunction, gout, suprarenal gland failure, hypercalciuria or nephrocalcinosis - History of hypersensitivity to the investigational medicinal products or to any drug with similar chemical structure or to any excipient present in the pharmaceutical form of the investigational medicinal products |
| Trial duration and dates | First subject in: July 2010  Last subject out: 31 August 2011  Duration of the trial 14months |
| Number of subjects | It is planned to enrol 60subjects |
| Number of sites | Monocentric study |
| Primary endpoint | Mean IOP reduction (∆IOP) three months after trabeculectomy in comparison to the mean preoperative IOP |
| Secondary endpoints | - Safety and tolerability of both treatment arms: Descriptive analysis of adverse events and questionnaires. - Number of necessary 5FU injections and suture lyses at Visit 5 - Required number of needlings and reoperations at Visit 5 - Change in IOP between Visit 1 and Visit 2 - Comparison between both groups of ocular hypotension rate (IOP 0-5 mm Hg, shallow anterior chamber, Descemet’s folds, choroid swelling, macular and choroidal folds) and filtration bleb classification in both groups at every postoperative visit. - Change in quality of life for the two regimens based on the NEI VFQ 25 quality-of-life questionnaire between Visit 1, Visit 2 and Visit 5 in both groups - Patients’ satisfaction (visual analogue scale) with pharmacologic intervention for IOP lowering - Change in status of conjunctiva |
| Statistical analysis | Change in IOP between baseline and three months post-OP was defined as the primary efficacy variable. A non-inferiority test on a one-sided level of significance α=0.025 will be carried out to show that treatment with Cosopt-S® b.i.d. (7:00 am, 7:00 pm; +/- 1 h) is not inferior to the reference preoperative treatment. Δ = 4 mm Hg was specified as the non-inferiority limit. The primary analysis will be conducted on the per protocol population. |

Trial schedule

| Visit  Action | Visit 1 Screening & Randomisation | Visit 2 | Surgery | Visit 3 | Visit 4 | Visit 5  (Primary  endpoint) | Visit 6 (optional  follow-up) |
| --- | --- | --- | --- | --- | --- | --- | --- |
| Trial day | -16 weeks to -28 days | Day -1 | Day 0 | Day 7±3 | Day 28±7 | Week 12±7days | Week 24±14 days |
| Demographics (sex, age) | **X** |  |  |  |  |  |  |
| Patient information and informed consent | **X** |  |  |  |  |  |  |
| Previous and concomitant diseases | **X** |  |  |  |  |  |  |
| Previous and concomitant treatments | **X** |  |  |  |  |  |  |
| Inclusion/exclusion criteria | **X** |  |  |  |  |  |  |
| Pregnancy Test (if applicable) | **X** |  |  |  |  |  |  |
| Laboratory tests (if applicable) | **X** |  |  |  |  |  |  |
| Trabeculectomy |  |  | **X** |  |  |  |  |
| Best-corrected visual acuity (ETDRS charts) | **X** | **X** |  | **X** | **X** | **X** | **X** |
| Non-contact Pachymetry |  | **X** |  | **X** |  | **X** |  |
| IOP | **X** | **X** |  | **X** | **X** | **X** | **X** |
| Optical Coherence Tomography |  | **X** |  | **X** | **X** | **X** | **X** |
| Axial length (IOL Master) |  | **X** |  |  | **X** |  |  |
| Anterior chamber depth (AC or IOL Master) |  | **X** |  | **X** |  |  |  |
| Photography (conjunctiva) | **X** | **X** |  |  |  | **X** | **X** |
| Slit lamp examination | **X** | **X** |  | **X** | **X** | **X** | **X** |
| Randomisation | **X** |  |  |  |  |  |  |
| Filtration bleb classification (Grehn) |  |  |  | **X** | **X** | **X** | **X** |
| Grading of conjunctiva (ORA redness scale) | **X** | **X** |  |  |  |  |  |
| Questionnaires  (Patients’ satisfaction, NEI VFQ-25) | **X** | **X** |  |  |  | **X** |  |
| Previous 5-FU injections and suture lyses |  |  |  |  |  | **X** |  |
| Previous needlings |  |  |  |  |  | **X** |  |
| Changes in medical health or concomitant medication |  | **X** |  | **X** | **X** | **X** | **X** |
| Adverse events |  | **X** |  | **X** | **X** | **X** | **X** |
| End of trial (final visit) |  |  |  |  |  |  | **X** |

Trial Administrative Structure

| Sponsor (according to §4 AMG) | Name University Medical Center  Johannes Gutenberg-University Mainz  Address [name]  [contact]  [contact]  e-Mail [[contact]](mailto:[contact]) |
| --- | --- |
| Sponsor’s legal representative | Name Univ.-[name]. [name]  Scientific Chairman of University Medical Center  Address [name]  [contact]  [contact]  e-Mail [[contact]](mailto:[contact]) |
| Coordinating / Principal investigator (according to §4 AMG) | Name [name], FEBO  Address Department of Ophthalmology,  Johannes Gutenberg-University Mainz,  [name]  [contact]  [contact]  e-Mail [contact] |
| Trial coordinator | Name [name], FEBO  Address Department of Ophthalmology,  Johannes Gutenberg-University Mainz,  [name]  [contact]  [contact]  e-Mail [contact] |
| Safety officer (SAE Management) Biometrician / Statistician  Data manager  Clinical monitor | Name IZKS Mainz  Address Johannes Gutenberg-University Mainz, [name]  [contact]  [contact] |
| Funding / grant | Name [name], MSD SHARP & DOHME GMBH  Address [name]  [contact]  [contact]  e-Mail [contact] |

TABLE OF CONTENTS

[1 Introduction 10](#__RefHeading___Toc197240606)

[1.1 Scientific background 10](#__RefHeading___Toc197240607)

[1.2 Trial rationale 10](#__RefHeading___Toc197240608)

[1.3 Treatments and rationale for dose selection 11](#__RefHeading___Toc197240609)

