## Secondary objectives

The secondary objective(s) of the trial are:

- Safety and tolerability of both treatment arms: Analysis of adverse events and questionnaires.
- Number of necessary 5FU injections and suture lyses at Visit 5
- Required number of needlings and reoperations at Visit 5
- Change in IOP between Visit 1 and Visit 2
- Comparison between both groups of ocular hypotension rate (IOP 0-5 mm Hg, shallow anterior chamber, Descemet’s folds, choroid swelling, macular and choroidal folds) and filtration bleb classification in both groups at every postoperative visit
- Change in quality of life for the two regimens based on the NEI VFQ 25 quality-of-life questionnaire between Visit 1, Visit 2 and Visit 5 in both groups
- Patients’ satisfaction with pharmacologic intervention for IOP lowering between Visit 1, Visit 2 and Visit 5 in both groups
- Change in the conjunctiva status between Visit 1 and Visit 2 in both groups

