## Efficacy analyses

All non-inferiority hypotheses will be tested on a one-sided level of significance α=0.025. All superiority hypotheses will be tested on a two-sided level of significance α=0.05.

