### Analysis of secondary endpoints

Two-sided significance tests with  = 0.05 will be carried out for the following secondary and tertiary efficacy variables on an exploratory basis: Change in IOP between Visit 1 and Visit 2 will be investigated by means of an ANCOVA model including the baseline value as a covariate. The number of necessary 5FU injections and sture lyses, needlings and reoperations as well as the change in vision development will be tested between groups by means of the Wilcoxon-Mann-Whitney test. The ocular hypotension rate will be compared by a Chi-Square test. The NEI VFQ 25 quality of life questionnaire (composite score and subscales) will be analysed by a linear model with repeated measurements. The same method is employed for the patients’ satisfaction. The ORA redness scale will be compared by the Wilcoxon-Mann-Whitney test. For the change in the filtering bleb classification descriptive statistics will be presented only.

All other target criteria and demographic, anamnestic and safety data will be analysed by descriptive statistical methods, i.e. quantitative data will be described by valid N, mean, standard deviation, minimum, median and maximum, qualitative and ordinal variables will be presented by means of distribution functions. Appropriate inferential statistical methods will be employed. All analyses of secondary endpoints will be interpreted purely exploratory.

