## Analysis of adverse events

All summaries and listings of safety data will be performed for the safety population.

Frequencies of subjects experiencing at least one adverse event (AE) will be displayed by body system and preferred term according to MedDRA terminology. Detailed information collected for each AE will include: A description of the event, duration, whether the AE was serious, intensity, relationship to trial drug, action taken, clinical outcome. Summary tables will present the number of subjects observed with AEs and corresponding percentages. Additional subcategories will be based on event intensity and relationship to trial drug.

A subject listing of all AEs will be prepared.

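### The synopsis sets out to show that Cosopt-S is descriptively superior on safety, while the body of the protocol treats safety neutrally and as exploratory

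*Protocol*

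**What the plan says.** The synopsis, under secondary objectives, gives the aim "To show that the tolerability and safety of COSOPT-S® b.i.d. is descriptively superior to that of reference therapy". The matching synopsis endpoint is "Safety and tolerability of both treatment arms: Descriptive analysis of adverse events and questionnaires".

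The body is neutral. Section 2.2 (Secondary objectives), and section 3.4 (Secondary endpoints) in the same terms, read "Safety and tolerability of both treatment arms: Analysis of adverse events and questionnaires", with no direction and no mention of superiority.

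On analysis, section 7.3.2 says "All other target criteria and demographic, anamnestic and safety data will be analysed by descriptive statistical methods", adds "Appropriate inferential statistical methods will be employed" without naming a method for safety, and closes with "All analyses of secondary endpoints will be interpreted purely exploratory". Section 7.4 covers AEs: "Summary tables will present the number of subjects observed with AEs and corresponding percentages". It names no between-arm contrast, interval, threshold or test, and no AE measure is among the variables that section 7.3.2 lists for testing. The NEI VFQ-25 and patients' satisfaction are on that list, with a repeated-measures linear model.

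**The concern.** To show superiority is to announce a conclusion. The neighbouring synopsis objectives are worded as a comparison and an exploration, and the body words the safety item as an analysis. The document therefore gives two accounts of its safety aim, one directional and one open.

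The directional account has no stated criterion. A reader who asks when the AE part of the objective has been met finds two columns of percentages, and the only thing those can yield without further rules is which one is lower. The sign of an observed difference carries no allowance for chance, and with 30 patients per arm chance is large.

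The stake is how the result may be described. The primary test can deliver only non-inferiority on intraocular pressure (IOP). Section 1.1 presents Cosopt-S as a way to avoid the known adverse effects of oral acetazolamide at comparable pressure reduction, and section 1.2 says the results should inform possible future recommendations. A report stating that better safety had been shown, on the strength of a numerical difference, would say more than the data can bear.

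**Working it through.** **The plan's own figure.** The protocol gives no error rate or power for safety. Its only sizing is for the primary test (section 7.1): margin 4 mm Hg, SD 5 mm Hg, one-sided 0.025, power 0.80, giving 26 evaluable patients per arm. This reproduces: the noncentral t calculation gives power 0.791 at 25 per arm and 0.807 at 26. Safety played no part in it.

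**Inputs for the check.**
- 30 patients per arm, 1:1 (section 3.2).
- AE rates: not given in the protocol. Assumed 10% to 80%.
- Readout: one proportion, subjects with at least one AE. Section 7.4 tabulates such frequencies; using the overall proportion as the deciding figure is an assumption.
- Rule examined: the Cosopt-S proportion is strictly lower than the reference proportion. This is inferred, not stated in the protocol.

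**No true difference.** Let X (Cosopt-S) and Y (reference) be independent Binomial(30, p). By symmetry

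P(X < Y) = (1 − P(X = Y)) / 2, with P(X = Y) = Σ P(X = k)² over k = 0 to 30.

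| Assumed AE rate p | P(tie) | P(Cosopt-S strictly lower) |
|---|---|---|
| 10% | 0.174 | (1 − 0.174)/2 = 0.413 |
| 20% | 0.129 | 0.436 |
| 30% | 0.112 | 0.444 |
| 50% | 0.103 | 0.449 |
| 80% | 0.129 | 0.436 |

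**Cosopt-S truly 10 points worse.** Here P(X < Y) = Σ P(X = i)·P(Y > i), with different rates in the two arms.

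| Cosopt-S v reference | P(Cosopt-S strictly lower) |
|---|---|
| 30% v 20% | 0.146 |
| 40% v 30% | 0.170 |
| 50% v 40% | 0.180 |

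**Precision of an interval instead.** The approximate 95% half-width for a difference in proportions, with the same rate p in both arms, is 1.96·√(2p(1 − p)/30).
- p = 20%: 1.96·√(0.32/30) = 0.202
- p = 30%: 1.96·√(0.42/30) = 0.232
- p = 50%: 1.96·√(0.50/30) = 0.253

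So the half-width is about 20 to 25 points for rates of 20% to 50%. A 10-point difference in either direction lies well inside it.

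**The case against.** The strongest reply is that the protocol already disarms the synopsis line. Section 7.3.2 makes every secondary analysis exploratory, the full statements of objectives and endpoints are neutral, and the word descriptively can be read as a disclaimer of inference. Section 7.3.2 also promises unspecified inferential methods, and section 7 leaves analysis detail to a statistical analysis plan that is not at hand. Much of this stands. It means that no confirmatory safety claim is available under the protocol, and that the absence of an interval in section 7.4 is not in itself an error. It does not remove the mismatch: an exploratory analysis cannot show superiority, and one line of the synopsis says that it should.

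Three stronger readings are tempting, and the documents support none of them.
- A reader might infer that the protocol lays down the direction of the difference as the decision rule. It does not. That is only the most natural reading of a line to which no criterion is attached.
- A reader might extend the argument to the questionnaires, or compute the chance that at least one of several readouts favours Cosopt-S. The NEI VFQ-25 and satisfaction scores have a planned model, so their sign alone is not the analysis. The protocol nowhere says that one favourable readout is enough. In addition, section 6.2.1.1 records a symptom that worsens by at least three grades as an AE, so the symptom survey partly feeds the AE count.
- A reader might see a breach of the rule "All superiority hypotheses will be tested on a two-sided level of significance α=0.05". That sentence sits under Efficacy analyses, while AEs have their own section, so it is not tied to safety.

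**Conclusion.** The point holds as a minor inconsistency in wording with a consequence for reporting. The synopsis sets a directional safety aim; sections 2.2, 3.4 and 7.3.2 set a neutral, exploratory one. If the synopsis line is read as a numerically lower AE proportion, a drug with no advantage meets it about 41% to 45% of the time, and a drug 10 points worse meets it 15% to 18% of the time. These figures rest on 30 analysed patients per arm, a single AE proportion, assumed rates (10% to 80% with no difference; 30% v 20% up to 50% v 40% when worse) and the inferred rule. The sample size and the primary IOP analysis are untouched.

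**What to change.** 1. In the synopsis, replace the safety objective with: To estimate the difference in tolerability and safety between the regimens (exploratory). This matches sections 2.2, 3.4 and 7.3.2.
2. In section 7.4, add the between-arm difference (Cosopt-S minus reference) in the proportion of subjects with at least one AE, with a two-sided 95% confidence interval. Report it for the preoperative treatment period (start of study drug to Visit 2) and also for the whole observation period. Both are needed because section 6.2.1.3 collects AEs from consent to Visit 6, so the overall figure mixes surgical and postoperative events with the tolerability of a four-week preoperative regimen.
3. State that no claim of superior safety or tolerability will be made from a numerical difference alone. A formal significance threshold on this measure is not needed: the trial was not sized for it, and the endpoint is exploratory.

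The cost is one reworded line and two intervals, with no new data or patients. The downside is that intervals of about ±20 to 25 points will show how little the trial can say about AE rates, so the sponsor may lose a favourable descriptive statement.

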# Introduction

## Scientific background

The most common cause of post-trabeculectomy filtration failure is postoperative scarring [1]. Long-term preoperative treatment with local antiglaucoma agents containing preservatives, usually benzalkonium chloride, leads to histologic changes of the conjunctiva, with increased numbers and activity of lymphocytes, monocytes, fibroblasts, and beaker cells. These changes may favor the development of filtration bleb scarring [2-4] and increase the rate of post-trabeculectomy filtration failure [5-7].

Given these considerations, Broadway et al. proposed discontinuing antiglaucoma drugs and treating patients preoperatively with local steroids. Many surgeons therefore prepare their patients for planned trabeculectomy by discontinuing local antiglaucoma drugs, controlling IOP with oral acetazolamide, and treating the eye with local steroids [8]. To date no study has investigated the benefits of this approach. Consequently, preoperative treatment differs significantly between centers. Results published to date are based on retrospective, not randomized or masked, investigations, which, moreover, did not use the latest generation of local antiglaucoma drugs [9].

To pave the way for elucidating this question, we conducted a retrospective study [10] with 26 glaucoma patients who were to undergo trabeculectomy. Thirteen patients were prepared four weeks before trabeculectomy by discontinuing use of local antiglaucoma drugs in the affected eye and controlling the IOP with oral acetazolamide. One week before the procedure the eye was treated with local steroids. The other group of patients continued to receive antiglaucoma drugs up to the time of the procedure.

Trabeculectomy was conducted in all patients with intraoperative application of mitomycin C. In addition, in cases where there were signs of scarring in the postoperative observation period 5-fluorouracil was injected subconjunctivally.

IOP reduction after 12 months was identical in the two groups. The use of antiproliferative substances may have influenced this result.

We conclude from this study that discontinuation of local antiglaucoma drugs and patient preparation does not reduce the success rate of trabeculectomy. The disadvantages of current preoperative preparation and pretreatment of patients may therefore outweigh the benefits for the procedure. Firstly, the use of oral acetazolamide and local steroids often raises the IOP, which can damage the glaucomatous optic nerve [11–13]. Secondly, intolerance reactions to oral acetazolamide given over a period of four weeks are common and may be accompanied by dizziness, reduced physical performance, gastric pain, nausea, diarrhea, taste disturbances, and paresthesia resulting from potassium depletion. Compliance must therefore be monitored. Often several IOP checks by the ophthalmologist, potassium level tests by the GP, and potassium replacement are necessary.

Preservative-free COSOPT-S® eye drops b.i.d now provide a possibility to reduce IOP preoperatively with the aim of avoiding postoperative excessive scarring and the known adverse effects of oral acetazolamide while achieving comparable IOP reduction and long-term outcomes.

This study will investigate comparability (non-inferiority) of medical benefits of two different IOP lowering pharmaceutical interventions prior to trabeculectomy comparing COSOPT-S® bid to oral acetazolamide plus dexamethasone.

## Trial rationale

No treatment guidelines exist for interventions for IOP-lowering prior to trabeculectomy. This study compares head to head two commonly used pharmaceutical regimes.
This trial will investigate whether the preoperative treatment has an influence on postoperative outcome (IOP and scarring), safety and tolerability of the two interventions, whether patients prefer one of both tested therapies and health economic aspects. The results of this study will contribute a scientific basis to potential future recommendations for pharmacologic IOP-lowering interventions prior to trabeculectomy.

